## 4. STUDY POPULATION

### 4.1 Population (base)

All patients with gastro –intestinal carcinoma, who are diagnosed in the Amphia Hospital, Breda (clinically or outpatient clinic), will be discussed during a multidisciplinary meeting with gastroenterologist, GI- surgeon, radiologist and pathologist. Final treatment agreement and advice (if patient will be operated on) is made during this meeting.

All patients with aortic abdominal aneurysm, who are diagnosed in the Amphia Hospital, Breda (clinically or outpatient clinic), will be discussed during a multidisciplinary meeting with vascular surgeons and radiologist. Final agreement, if operation is needed, is made during this meeting.

During these meetings patients are selected to be included in our study. Next, either a gastro-enterologist or vascular surgeon will give written and spoken explanation about the study to obtain informed consent.

All patients of 70 years or older will be included in this study and seen at the 70 **PLUS** outpatient clinic. Both patients fit to wait for 5 weeks until surgery and patients who must be electively planned within 5 weeks will follow the pre-operative clinical pathway. (see figure).

This is done to obtain the best comparable population, in comparison with the retrospective population in which all patients are included with elective planned surgery of  $\geq 70$  years old

**Flowchart Inclusion of patients**

[figure not shown]

We assume to be able to include 275 patients over a period of two years, starting 1 January 2016 until 31 December 2017. About 20% of these patients will be included for an abdominal aortic aneurysm and 80% for gastro –intestinal carcinoma. [1]

### Inclusion criteria

In order to be eligible to participate in this study, a subject must meet all of the following criteria:

- all patients of 70 or older;
- all Ethnicities;
- male or female;
- patients who will be operated on due to colorectal cancer or abdominal aortic aneurysm;
- only primary surgery, or patients who had abdominal surgery more than one year ago;
- the surgical procedure can be laparoscopic, open or EVAR;
- the surgical procedure can be curative or palliative;
- patient or attorney –in –fact are capable to give written informed consent.

**Exclusion criteria**

A potential subject who meets any of the following criteria will be excluded from participation in this study:

- all patients with moderate to severe cognitive impairment or dementia in medical history;
- emergent surgery (clinical conditions that mandate a surgery within 12 hours of admission);
- urgent surgery (clinical conditions that mandate surgery between 12 and 72 hours of admission);
- patients not willing to participate or to fill in the questionnaires;
- all patient who do not speak Dutch or English.

*Demented patients*

Demented patients are included as a subgroup. Demented patients are important to optimise due to their fragile state, functional dependency and poor nutritional status.

This patient group will undergo the same treatment as non-demented patients. However, we will take into account the capability of the patient to answer questionnaires and undergo the exercises. This will all be done in firm consultation with the first care giver. Informed consent is asked to the patient and first care giver.

However, severe demented patients are rarely operated on in case of AAA or CRC. The risk in these patients in elective setting is very high compared to the benefits, also these patient usually start having complaints in worse case and are often operated on in acute setting (which is an exclusion criterion in this study).

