The historical patient group is based on patients admitted to the Amphia Hospital Breda in 2013 till November 2015. All data is gathered retrospectively but due to the use of the electronic patient file (Hyperspace Version IU4 (Epic, Inc., Verona, WI)) data was saved prospectively. No recent major changes have been made to indicate new procedures or pathways for the interventional care group compared to the historical patient group. The historical group will be comparable to the interventional care group in age ( $\geq 70$  years), ethnicity, gender and indication for surgery. Patients with emergent or urgent surgical intervention won't be included in this study, neither in the historical cohort. All patient who underwent neo adjuvant chemo – and / or radiotherapy are included.

However no questionnaires are undertaken in the historical group, hence the lack of prospective knowledge concerning dementia (scored by MMSE), quality of life or depression scale.

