## 8 STATISTICAL ANALYSIS

Standard procedure will be followed for descriptive statistics. The primary analysis for incidence of delirium will be a logistic regression model with adjustment for prognostically important covariates: age, gender, surgical history, comorbidity, (cardiac, pulmonary, neurological, renal, dementia, diabetes), use of medication, smoking status, use of alcohol, social economic status, use of glasses or hearing impairment, BMI, home situation. We will also consider the POSSUM score and Charlson comorbidity score. Repeated measure analysis will be applied for measurement over time during follow up. Historic and prospective patients will be selected for analysis fulfilling the same set of inclusion criteria. Missing data will be studied for specific patterns of occurrence, and multiply imputed. Statistical analysis was performed with IBM SPSS statistics software (SPSS Inc., Chicago, Illinois, USA).

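### The protocol both excludes and includes patients with dementia, so the two cohorts can be selected differently on a predictor of the primary outcome

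*Protocol*

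**What the plan says.** The Exclusion criteria open with a binding rule: "A potential subject who meets any of the following criteria will be excluded from participation in this study". The first criterion is "all patients with moderate to severe cognitive impairment or dementia in medical history". A paragraph on demented patients follows under the same heading. It states "Demented patients are included as a subgroup" and "This patient group will undergo the same treatment as non-demented patients", with allowance for what each patient can manage in questionnaires and exercises. On severity it says only that "severe demented patients are rarely operated on in case of AAA or CRC". The exclusion criterion it names at that point is acute surgery, not dementia. The Inclusion criteria accept that "patient or attorney –in –fact are capable to give written informed consent".

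Elsewhere, dementia is listed among the baseline characteristics and predictors of delirium (section 6.2, OUTO Care) and among the covariates of the primary logistic regression (section 8).

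Section 4.1 describes the historical controls as all electively operated patients aged 70 or older. Section 3 calls them comparable in age, ethnicity, gender and indication, without naming dementia. It adds that no questionnaires were taken in that group, "hence the lack of prospective knowledge concerning dementia (scored by MMSE), quality of life or depression scale". Section 8 says: "Historic and prospective patients will be selected for analysis fulfilling the same set of inclusion criteria".

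**The concern.** A recruiter, or an analyst building the control group, who finds a dementia diagnosis in the record is told both to exclude that patient and to include the patient as part of a subgroup. In a randomised trial an unclear eligibility rule would touch both arms alike. Here a prospective cohort is compared with past patients, and the two are assembled by different routes. If one route follows the exclusion bullet and the other follows the subgroup paragraph, the cohorts differ in the share of patients with dementia. Because dementia is a listed predictor of delirium, part of any difference in delirium incidence would then come from selection and not from the programme.

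**Working it through.** **1. Can both statements be followed?**

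- Exclusion bullet: dementia in the medical history means out, and meeting any one criterion is enough.
- Subgroup paragraph: demented patients are in and are treated like the others, with no severity limit.
- The possible bridge is that *moderate to severe* also qualifies *dementia*, so that only mild dementia is included. The text never says mild. It explains the scarcity of severe cases by surgical practice and acute presentation, not by the bullet. The bridge is not written.
- Proxy consent and the dementia covariate fit inclusion. The bullet does not.

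**2. Does section 8 settle it?** No. It requires the same criteria for both cohorts, but the rule to be shared contradicts itself.

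**3. The plan's own sample size.** Inputs (Sample size calculation): 15% versus 7.5%, 80% power, two-sided 5%, equal groups. With the unpooled variance formula:

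n = (1.960 + 0.842)² × (0.15×0.85 + 0.075×0.925) / 0.075² = 274.7, so 275 per arm.

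This reproduces the stated figure. The pooled-variance version gives 278, and power at 275 is then 79.6%. The calculation is sound for the rates given.

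**4. How large could the distortion be?** The documents give neither the prevalence of dementia nor the delirium rate among these patients, so every input below except the 15% and the 7.5-point target is an assumption. Suppose the programme has no effect, the controls include demented patients and have 15% delirium overall, and the prospective cohort has no demented patients.

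(a) With prevalence d and delirium rate r in dementia, the rate among the rest is (0.15 − d·r)/(1 − d):

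| d | r | Rate in the rest | Spurious reduction | Share of 7.5 points |
|---|---|---|---|---|
| 3% | 40% | 14.2% | 0.8 points | 10% |
| 5% | 50% | 13.2% | 1.8 points | 25% |
| 8% | 60% | 11.1% | 3.9 points | 52% |

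(b) With prevalence d and relative risk RR, the rate among the rest is 0.15/(1 − d + d·RR):

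| d | RR | Rate in the rest | Spurious reduction | Share of 7.5 points |
|---|---|---|---|---|
| 2% | 2 | 14.7% | 0.3 points | 4% |
| 5% | 3 | 13.6% | 1.4 points | 18% |
| 10% | 4 | 11.5% | 3.5 points | 46% |

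The two forms together span 0.3 to 3.9 points. The delirium rates in (a) imply relative risks of 2.8, 3.8 and 5.4, so its last row is more extreme than anything in (b).

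**5. Opposite selection.** If demented patients are enrolled prospectively but removed from the controls, and the 15% now stands for the prospective mix, the same sizes apply with the sign reversed. The programme would look worse than it is.

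**6. What excluding these patients from both cohorts would do to power.** On the 5%/50% assumption the control rate becomes 13.2%, and halving it gives 6.6%. The unpooled formula then needs about 319 per arm. With 275 per arm power is about 74%. Removing 5% leaves 275 × 0.95 ≈ 261 per arm and about 72% power, against 80% planned.

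**The case against.** The strongest defence is that the protocol has two safeguards: the same criteria for both cohorts, and dementia in the primary model. If the subgroup paragraph is followed in both, this conflict creates no selection bias at all. The second safeguard has real value. If dementia history is recorded equally well in both cohorts, adjustment takes away much of the crude difference in step 4. The first is only as good as the rule it refers to, and that rule is the one in conflict.

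Three stronger readings are tempting and are not supported.

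- *That patients are excluded on an MMSE score the controls never had.* The bullet refers to the medical history, which is a record criterion. In section 6.2 a low MMSE leads to geriatric assessment, not exclusion. The controls lack questionnaires, but section 3 says their data were saved prospectively in the electronic file. Dementia history is therefore not shown to be unavailable for them.
- *That the bias favours the programme.* This needs exclusion prospectively and retention in the controls. Proxy consent and the allowance for limited capability point towards prospective enrolment.
- *That the figures in step 4 estimate the bias.* They are crude, assume complete removal from one cohort only, and give no credit to the covariate. The remark that severe dementia is rarely operated on argues against the upper end.

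**Conclusion.** The contradiction is certain and stands in current text. It leaves open whether patients with documented dementia belong in either cohort, and so permits unequal selection on a predictor of the primary outcome in a historically controlled comparison. Whether that happens, in which direction and by how much cannot be determined from the documents. The range of 0.3 to 3.9 points shows only that the possible distortion runs from negligible to about half the target effect before adjustment, on assumed prevalence and risk. The sample size formula is not in error, although the 15% control rate depends on which dementia rule the historical cohort follows. The rule should be settled before the analysis cohorts are defined.

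**What to change.** Reconcile the bullet and the subgroup paragraph into one dementia rule, ascertained in both cohorts from entries in the medical record made before the surgical indication, and applied identically.

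- **Simplest form**, which fits the proxy-consent criterion, the subgroup paragraph and the covariate list: delete dementia and cognitive impairment from the exclusion criteria, keep documented dementia history as a covariate in both cohorts, and report a sensitivity analysis that leaves these patients out of both. Cost: protocol wording, a check of the control records for dementia history, and one extra analysis. The planned sample size stands.
- **If the sponsor prefers exclusion**: remove the subgroup paragraph, apply the same record-based exclusion to the controls, drop dementia from the covariates, and restate the control rate and power for the remaining population. This is not only a change of wording. On the 5%/50% assumption, power falls to about 72% with 261 per arm, and about 319 per arm would be needed to restore 80%.

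In either case section 8 should refer to inclusion and exclusion criteria together, and name the dementia rule as one of those shared by both cohorts.

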**Sample size calculation**

To reduce the percentage of delirium from 15% to 7,5%, with a power of 80% with 5% two-sided significance level, a 50 -50 trial, needs 550 patients, or 275 patient per study arm.

We propose to make a comparison to a retrospective control group of patients studied between 2012 and 2014 in the Amphia Hospital, Breda. [1]

We aim to include 275 patients in the prospective study, which is feasible during approximately 2 years of accrual.

## 5. TREATMENT OF SUBJECTS

This prospective study is set up as an outpatient clinical pathway in which we intend to intervene in the usual pathway until operation. Within one week after setting indication for surgery, patients will be assessed. A nurse practitioner, a dietician and a physiotherapist will see the patients and if necessary a geriatrician will be involved (specific criteria for consulting dietician or geriatrician are defined in chapter 6.2 *Study procedures*).

In the usual pathway, patients are seen by the surgeon and are planned for surgery as soon as possible (which is the case in the retrospective group).

### Investigational product/treatment

Laboratory results to evaluate haemoglobin for intravenous iron (IVI), electrolytes for suppletion and nutritional status for refeeding.

Dietician's advice or refeeding products in patients with malnutrition.

Physical exercise for all patients and keeping a daily diary.

In case a geriatrician is consulted, they will assess if preventive interventions for delirium are needed (e.g. starting haloperidol).

### Use of co-intervention

Intra venous Iron–injection (Vifor Pharma) will be given in all anaemic patients, similar to the usual protocol for anaemic patients. (Addendum)

Anaemia was defined as a haemoglobin level of  $< 7.4$  mmol/L ( $< 120$  g/L) for women and  $< 8.1$  mmol/L for men ( $< 130$  g/L). In addition the WHO defines severe anaemia as a haemoglobin of  $4.4$  mmol/L ( $< 70$  g/L) and very severe anaemia as a haemoglobin of  $2.5$  mmol/L ( $< 40$  g/L). [8] [9]

If anaemic patients are using oral medication for iron deficit, they should stop this medication one day before starting intra venous iron –injection. Addendum: protocol Iron –injection in Dutch

### Escape medication

Escape medication for intra venous iron–injection are

- Adrenaline (1mg, 1ml) subcutaneously;
- Tavegyl (1 mg) oral or Tavegyl (2 mg) intra-venous;
- Dexamethason (4 mg, 1 ml) intra-muscular.

## **6. METHODS**

### **6.1 Study parameters/endpoints**

#### **Main study parameter/endpoint**

Our main parameter is the incidence of a delirium is screened by DOS scores and confirmed by DSM IV classification. [10] Duration in days of the delirium will be investigated.

Our main endpoints are mortality within one year and follow up till 12 months after surgery.

#### **Secondary study parameters/endpoints (if applicable)**

Secondary we will measure complication rate, hospital stay, ICU admission, and ICU duration of stay.

#### **Other study parameters (if applicable)**

At the moment of inclusion, all patient characteristics will be investigated including all factors of frailty causing delirium. These parameters will be investigated to indicate their relation with the incidence of delirium. [1, 7, 11-13]

## 6.2 Study procedures

### Standard Care

Standard pathway until surgery contains a visit to the outpatient clinic of either a gastroenterologist or a vascular surgeon to diagnose patients' condition. Patients will be discussed during multidisciplinary meeting, where the decision to operate is made. Next patient will be seen by their surgeon give explanation about the surgical procedure and to screen if patient is fit for surgery. Normal surgical preparations are done. At admission patient will be screened for delirium by a ward nurse. If necessary a dietician or geriatrician will visit. Standard care during admission is applied. (Addendum *Amphia protocol Colenchirurgie*)

### OUTO Care

For all patients of  $\geq 70$  with surgical indication for colorectal cancer or abdominal aortic aneurysm, the clinical pathway 70 PLUS outpatient clinic is set up in our surgery department.

During this pathway, we will screen for delirium and actively investigate and tackle their factors of frailty. The complete assessment en study procedure is described underneath (see figure).

[figure not shown]

Timeline OUTO pathway.

\* Quality guidelines SONCOS for colorectal carcinoma.

When patients arrive at the 70PLUS outpatient clinic (T1) a VNP will assess all base-line characteristics and predictors of delirium; age, gender, surgical history, comorbidity (cardiac, pulmonary, neurological, renal, dementia, diabetes), use of medication, smoking status, use of alcohol, social economic status, use of glasses or hearing problems, BMI, home situation and psychological history.

Burden of comorbidity is quantified using the Possum score, Charlsonn morbidity score and the American Society of Anesthesiologist score (ASA).[12, 14, 15]

The following questionnaires will be taken for cognition and mental health [16-18]:

- WHOQOL-BREF is used to determine quality of life;
- Mini mental status exam (MMSE) to assess cognitive dysfunction.

All patients will visit the physiotherapist, to assess patients' condition and strength using the following tests:

- Time Up and Go test (TUG test); [19]
- Timed chair stand test;
- The maximum inspiratory pressure (MIP) (using MicroRPM™, PT Medical);
- Gait speed using the 10 meter walking test [20];
- The hand force (using Hydraulic Hand dynamometer, JAMAR™);

The KATZ – ADL score is a standard test used in all patients admitted in our hospital to assess dependency and function at home.

Laboratory results measured during workup for diagnosis were used. If not investigated during work up additional blood will be drawn to complete our lab results.

Laboratory results used for this study are:

- haemoglobine, hematocrite;
- erythrocytes, thrombocytes;
- INR;
- Electrolytes (Sodium, potassium, chloride);
- Renal function (kreatinine, GFR, ureum);
- Liver functions (ASAT, ALAT);
- Lipid spectrum;
- Vitamine B, D and folic acid and prealbumine.

Anaemic patients (haemoglobuline level of < 7.4 mmol/L(<120 g/L) for women and < 8.1 mmol/L for men (<130 g/L)) will be given iron–injection after they filled in the WHOQOL-Bref. These patients will be admitted at day-care, which is standard care for all patients operated on with anaemia. [21] For the patients operated on in case of abdominal aortic aneurysm iron-Injection is part of this new pre – operative pathway and not former standard care.

Dietician is consulted when patient lost weight without purpose or lost appetite.

Nutrition is quantified using BMI, the minimal nutritional assessment test (MNA) and SNAQ -RC score. Also prealbumine is tested in the laboratory results.

Complete geriatric assessment is done for patients with the following criteria:

- MMSE score < 24 points;
- MMSE score < 26, If patient went to secondary school or university;
- delirium in medical history;
- polypharmacy:
  - Colorectal patients with more than 4 different kinds of medication
  - Vascular patients with more than four different kind of medication next to regular vascular preventive medication (Anti-coagulants, a statin, or bloodpressure medication)
- Time –up and Go Test (TUG Test) of ≥ 15 seconds.

Geriatrician will assess if preventive medication, like Haloperidol, is necessary.

The Care giver strain index (CSI) will be used to investigate pressure of first care giver during the course of illness of the patient.

At hospital admission (T2) patients will be seen by the same physiotherapist and researcher.

The physiotherapist will assess patients' condition and function using the TUG test, MIP, and 10 meters walk test.

The same laboratory results will be measured. The outcome of the WHOQOL–Bref can be aberrant if patients endure depressive feelings. This is why we will screen for depression, using

CES D-16 questionnaire at admission.

During admission a physician will see all patients on a daily basis. A nurse, while providing regular daily care, will screen for a delirium using the Delirium Observation Screening Score (DOSS) three times a day. DOSS is a shortened version with 13 items and is scored three times a day. A delirium is highly presumable if the patient had a DOSS of  $\geq 3$  and scored three times in a row. When delirium is suspected a geriatrician will be consulted to confirm the diagnosis using the DSM-IV criteria. [10] Also nurses will daily examine the level of pain using the Visual Analogue Score (VAS).

Data about the surgical procedure will be gathered. American Society of Anaesthesiologists' (ASA) classification for physical health is determined before surgery from history and physical examination by the attending anaesthesiologist. Anaesthesia time will be calculated as the duration between tracheal in- and extubation. Also blood loss during surgery and complications during surgery will be noted. All Patients undergoing surgery for colorectal carcinoma or abdominal aortic aneurysm surgery will receive general anaesthesia. Epidural anaesthesia is used as an adjunct as part of the fast track protocol. If patient is not eligible for epidural anaesthesia is not eligible (in case of allergies or coagulopathy), a Patient-Controlled Analgesia pump (PCA-Pump) with Morphine will be used as an alternative. Patients operated on with EVAR will not receive an epidural or a PCA. Other parameters gathered during admission, are complication, ICU stay, transfusion of packed cells, and mortality. Complications are classified using the Clavien –Dindo classification of surgical complications. [22]

At discharge (T3) patients will fill in WHOQOL-Bref, MMSE will be taken, the same blood will be drawn and the CSI will be filled in by first caregiver.

At follow up after six months (T4) and 12 months (T5) WHOQOL-Bref, CSI, MMSE and CESD-16 will be taken. Also function is tested using the TUG test and KATZ – ADL.

Table 2 describes when measurements are repeated to evaluate the effects of the intervention before surgery and after surgery. Laboratory results and physical exercises will be measured at admission.

Addendum describes all questionnaires, patient's chart, and laboratory results.

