### **6.7 Premature termination of the study**

Study will be terminated in case of a higher complication rate or mortality compared to former research done. [1] After one year, analysis will be done to investigate if no negative effect occurs due to this study, this is done by comparing complication rate, incidence of delirium, rate of ICU admission, length of hospital stay and mortality within 6 months, with the historical patient group.

Also we will investigate the use and efficiency of iron injection in anaemic patients.

Interim analyses are not possible due to the small amount of patients gathered. No significant data can be obtained.

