### **7.2 AEs, SAEs and SUSARs**

#### **Adverse events (AEs)**

Adverse events are defined as any undesirable experience occurring to a subject during the study, whether or not considered related to trial procedure. All adverse events reported spontaneously by the subject or observed by the investigator or his staff will be recorded.

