## **10. ADMINISTRATIVE ASPECTS, MONITORING AND PUBLICATION**

### **10.1 Handling and storage of data and documents**

All data will be gathered in the electronic patient file using Hyperspace Version IU4 (Epic, Inc., Verona, WI).

A specific OUTO-study folder is created in which data is only accessible to the sponsor (LLA) and researcher (CM). A code number for each patient will be used. This folder is secured and the code is safeguarded by the researcher (CM) and sponsor (LLA). Questionnaires are securely safeguarded by the researcher and locked.

VSP, dietician, physiotherapist and geriatrician are able to fill in all data in the OUTO-study folder during patient contact.

Patient's physician or practitioner is able to see patients electronic file.

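### In-hospital complications are gathered by one process in OUTO and another in the historical controls, with no common definition, source or grading rule, so the comparison is at risk of ascertainment bias against OUTO

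*Protocol*

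**What the plan says.** **Role of the outcome.** Protocol section 2 aims to reduce postoperative complications relative to a retrospective database. The secondary endpoints in section 6.1 and section 8.2 list complications, and section 8.2 limits them to the hospital stay.

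**OUTO cohort.** Under OUTO Care in section 6.2: "Other parameters gathered during admission, are complication, ICU stay, transfusion of packed cells, and mortality". The next sentence grades complications by Clavien-Dindo. Section 10.1 adds: "A specific OUTO-study folder is created", which pathway staff can fill in during patient contact. Section 7.2 says of adverse events: "All adverse events reported spontaneously by the subject or observed by the investigator or his staff will be recorded".

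**Control cohort.** Section 3 says: "All data is gathered retrospectively". The same sentence adds that the entries were saved prospectively because an electronic patient file was in use. The Standard Care text in section 6.2 describes no complication recording or grading.

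**What is made equal.** Section 8 applies the same inclusion criteria to both cohorts. Sections 3 and 10.1 name the same electronic file system for both. No section applies one complication definition or grading rule to both.

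**Use of the result.** Section 6.7 says: "Study will be terminated in case of a higher complication rate or mortality compared to former research done". Its next sentence plans a one-year comparison of several outcomes, complication rate among them, with the historical group.

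**The concern.** When one cohort's events are noted as they happen and the other's are read back from routine notes, the difference in observed rates mixes the treatment effect with the difference in recording. Deaths and ICU admissions are likely to be on file in either period. Minor complications depend more on whether somebody wrote them down. If control files miss more of them, OUTO looks worse than it is.

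Two things are at stake. A real reduction in a stated secondary aim could be hidden. And section 6.7 speaks of a higher complication rate without a margin or test, so even a modest recording difference could push the one-year check in the wrong direction.

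This is more than detail left to an analysis plan. The protocol fixes how OUTO complications are gathered, and no later analysis can recover control events that were never written down. What can still be chosen is a source that both cohorts share.

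**Working it through.** **The plan's own figure.** The protocol gives no calculation for complications. Its only sample size is for delirium: "To reduce the percentage of delirium from 15% to 7,5" per cent, "with a power of 80% with 5% two-sided significance level", "needs 550 patients, or 275 patient per study arm". With unpooled variance, n = (1.96 + 0.8416)² × (0.15 × 0.85 + 0.075 × 0.925) / 0.075² = 274.7, so 275 per group. The pooled formula gives 278. The figure reproduces and is not in dispute; it is used here only for group sizes.

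**Inputs for the illustration**
- From the protocol: 275 per group, and OUTO accrual of 275 over two years, so about 137 OUTO patients after one year (275 / 2 = 137.5).
- Assumed, not in the protocol: true complication risk p of 30-40%, equal in both cohorts; capture c_O of 95-100% in OUTO and c_C of 80-90% in controls; steady accrual; all 275 controls available at the one-year look.

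**Formulas.** Observed rates are a = p × c_O and b = p × c_C, so the spurious difference is p × (c_O − c_C).

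SE = √[a(1 − a)/n_O + b(1 − b)/n_C], and P(OUTO numerically higher) = Φ[(a − b)/SE].

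P(significantly higher, two-sided 5%) = 1 − Φ[(1.96 × SE₀ − (a − b))/SE], where SE₀ is the pooled standard error.

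**Smallest gap** (p = 0.30, capture 95% v 90%): a = 0.285, b = 0.270, difference 0.015.
- 275 v 275: SE = 0.0382, z = 0.39, P(higher) = 0.65, P(significantly higher) = 0.06.
- 137 v 275: SE = 0.0470, z = 0.32, P(higher) = 0.63.

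**Largest gap** (p = 0.40, capture 100% v 80%): a = 0.40, b = 0.32, difference 0.08.
- 275 v 275: SE = 0.0408, z = 1.96, P(higher) = 0.98, P(significantly higher) = 0.50.
- 137 v 275: SE = 0.0504, z = 1.59, P(higher) = 0.94.

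| | Equal capture | Assumed capture gap |
|---|---|---|
| Spurious difference, points | 0 | 1.5 to 8 |
| P(higher), 275 v 275 | 0.50 | 0.65 to 0.98 |
| P(higher), 137 v 275 | 0.50 | 0.63 to 0.94 |
| P(significantly higher), 275 v 275 | 0.025 | 0.06 to 0.50 |

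**Masking.** With full capture in OUTO, the apparent risk ratio is the true ratio divided by c_C. A true ratio of 0.80 with c_C = 0.80 appears as 0.80 / 0.80 = 1.00, so the benefit vanishes.

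**The case against.** The strongest reply is that the source is largely shared already. Both cohorts come from one hospital and one electronic file system, and section 3 says control entries were made prospectively. This stands and limits the likely gap. It does not close it, because a shared file does not guarantee the same prompting to record, and nothing says control complications are defined or graded in the same way.

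Four stronger readings are tempting, and the protocol does not support them.

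- *Every spontaneously reported event counts as a complication in OUTO.* Section 7.2 is a safety-reporting rule. Nothing says that adverse events feed the complication outcome, which section 8.2 confines to the hospital stay. The protocol does not expressly keep the two apart either, so the fix should.
- *Study staff record OUTO complications.* The OUTO Care text names no recorder, and section 10.1 does not say that surgical complications go in the study folder.
- *The comparison is biased.* Neither the existence nor the size of under-capture in controls can be shown from the document. It is a risk.
- *Under-recorded controls directly trigger termination.* The termination sentence compares with former research. The historical-group comparison is in the sentence after it, and its link to stopping is only implied. With no margin, a rule read literally would be met about half the time under no effect even with equal capture. That is a separate weakness.

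It is also fair to say that the protocol does not state that all Clavien-Dindo grades are pooled into one rate; how grades are summarised may properly be left to an analysis plan.

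**Conclusion.** The point holds as a risk of ascertainment bias in a secondary outcome that also enters the one-year check. The protocol describes different collection processes for the two cohorts and makes only the inclusion criteria, the hospital and the file system common. If controls are under-recorded, the error runs against OUTO.

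The 1.5 to 8 points and the probabilities above rest wholly on assumed risks and capture fractions; with equal capture the excess is zero. They show that plausible recording gaps could matter at these sample sizes, not that such gaps exist. The primary outcome and its sample size are untouched by this point. A correction is worth making because it is cheap and the result may bear on continuing the study.

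**What to change.** Add to sections 6.2 and 8.2, and refer to it from the one-year check in section 6.7: for the between-cohort comparison, in-hospital complications in both cohorts are taken from the same routine electronic-file fields, under one written definition, one window (the hospital stay) and one Clavien-Dindo coding rule. State that the OUTO study folder and the adverse event log are not sources for this comparison. They continue to serve their own purposes.

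Report grade III or higher alongside all grades, as a sensitivity analysis less dependent on recording habits. It need not replace the all-grade comparison, since the common rule already addresses the main problem and dropping lower grades would narrow a stated aim.

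The cost is a paragraph of wording and one extraction rule applied to both sets of files. The small downside is that some minor events recorded only in OUTO study records leave the comparison. Any remaining difference in what ward staff wrote in the two periods would not be removed and should be acknowledged when the result is reported.
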